##### Screening tools

The Mini-Mental State Examination [35] will be used to assess the cognitive function of the PMCI/MD and determine their eligibility for participation. There is a great heterogeneity among studies regarding the cutoff scores for dementia and mild cognitive impairment. The most common scores are ranging 23 to 27, however, a person’s age and educational level determines the accuracy of this cut-point.

The Short Form of the Geriatric Depression Scale [36] will be used to rule out depressive pseudo-dementia which is considered a reversible form of cognitive deficit. PMCI/MD scoring over 11 will not be eligible for participation.

##### Covariables

Covariables will be Sociodemographic data (marital status, level of education, living arrangements and hobbies) and Medical history (smoking habit, disabilities, anthropometric data, cognitive impairment data, comorbidities and need for vital sign monitoring).

##### User-behaviour

A user-behaviour analysis will be performed to assess how users interact with the platform and how their behaviour affects its effectiveness. We will assess and analyze the frequency of access to the platform itself and to each functionality and the length of each interaction. These data will be correlated with users’ reminder schedules to explore differences between proactive and reactive use of the platform and will be followed up over time to understand how increasing familiarity with the platform affects user-behaviour. Additionally, interviews will be scheduled with 5% of randomly selected users after 12 months of using the platform to assess their user experience.

##### Usability evaluation

The System Usability Scale (SUS) [37, 38] will be used to address how well patients learn and use TV-AssistDem. It is a simple, 10-item scale giving a global view of subjective usability. The respondent indicates the degree of agreement or disagreement with each statement on a 5-point Likert scale with a score range of 0 to 100. The SUS scale will be used after the patients have had an opportunity to use TV-AssistDem before any debriefing or discussion takes place at 6 and 12 months.

The collected variables and data collection time are presented in Tables 1 and 2.

**Table 1 Tab1:** Patient’s data collection table

Assessment	Outcome variable	Screening	Baseline	6 months	12 months
Informed Consent	NA	X			
Capacity to Consent	NA	X			
Mini-Mental State Examination	NA	X		X	X
Geriatric Depression Scale	NA	X		X	X
Sociodemographic data	NA		X	X	X
Medical history	NA		X	X	X
Quality of Life-Alzheimer’s Disease Scale	Primary		X	X	X
EuroQoL-5D-5 L	Secondary		X	X	X
Medication Assessment Questionnaire	Secondary		X	X	X
Lawton Instrumental Activities of Daily Living Scale	Secondary		X	X	X
Client Service Receipt Inventory	Secondary		X		X
System Usability Scale	NA			X	X

*NA* = non-applicable

**Table 2 Tab2:** Caregiver’s data collection table

Assessment	Outcome variable	Screening	Baseline	6 months	12 months
Informed Consent	NA	X			
Caregivers data	NA	X			
Quality of Life-Alzheimer’s Disease Scale	Primary		X	X	X
EuroQoL-5D-5 L	Secondary		X	X	X
Zarit Burden Interview	Secondary		X	X	X
Lawton Instrumental Activities of Daily Living Scale	Secondary		X	X	X

*NA* = non-applicable

### Intervention and control group

#### Intervention group

Intervention will consist in the use of TV-AssistDem: an interactive platform which offers remote assistive services through a device connected to the television. Patients and caregivers have been actively involved in designing the 6 main functionalities of this innovative technology. Adapting the functionalities and content to best fit PMCI/MD and their caregivers has been crucial. Focus groups have been carried out and valuable indications have been gathered for the platform development. The TV-AssistDem prototype will be validated through a pre-pilot feasibility study which will include a User acceptance report.

The product consists of an Android software and hardware TV (a Digital TV Set Top Box with Android technology) designed to provide tele-care services at home using the TV. The system consists of (Fig. 1):
A Set Top Box which allows end-users to enjoy TV-AssistDem services. It’s based on ARM chipsets with Android operating system and a digital TV tuner (optional, including HDMI pass-through) compatible with DVB-T/T2 (European version).A webcam which enables the videoconference service.A centralized back-end server which is responsible for managing and storing information about patients and providing the basic functionalities needed for TV-AssistDem services.A web-based user interface which allows researchers to manage general information, events and appointments concerning the associated primary patients.

**Fig. 1 Fig1:**
[figure not shown]
TV-AssistDem system

This platform has three core services and three service-oriented applications (Fig. 2).

**Fig. 2 Fig2:**
[figure not shown]
Main menu functionalities

##### Core services

The set of core services is composed by general communication functionalities and other specific functionalities that will allow the system to collect user information.
Calendar and reminders: Enables the dyad to schedule health related events such as daily health care or prescribed treatment (e.g. medication dose and time), ADLs (e.g. physical activities), celebrations (e.g. family birthdays and holidays) etc. On-screen messages appear to remind events while the patient watches the television.Health monitoring and data transmission to a health server: Records vital sign measurements such as blood pressure, pulse, glucose and weight and displays evolution in charts. This information will be automatically transmitted from the platform to a health server which researchers and caregivers will have access to.Videoconference: Allows bidirectional communication between patients and their caregivers or researches. Researches connect to the platform from a remote station for health monitoring and remote assistance and support, as well as distance health learning. Caregivers connect to the platform from a mobile device App or PC for social interaction.

##### Service-oriented applications

The set of service-oriented applications is composed by more specific functionalities that aim at stimulating cognition, accessing personal media and useful healthcare information.
Cognitive stimulation: Includes specific software, Stimulus©, with a series of interactive exercises that train different cognitive processes [39]. These activities (+ 50) are classified around ten functional areas: attention, visual and auditory perception, working memory, long-term memory, calculation, reasoning, executive functions, visuomotor functions, language and processing speed. It is designed for tablet use but has been specifically adapted for TV-AssistDem.Reminiscences: Is a tool to create a personalized book of life, gathering memories of one’s self in the past using media (photos, videos and music).Healthcare education: Offers information and support resources on dementia and other chronic diseases for PMCI/MD and their caregivers: infographics, care guides and online videos.

Within one to two weeks after study inclusion and upon completion of the baseline assessments, patients assigned to the intervention group will be scheduled a TV-AssistDem installation and training visit. Following this visit, patients will receive weekly calls during the first month. The purpose of these calls is to encourage platform use and solve usage problems. A maximum of six calls will be made during the follow-up period depending on individual platform use.

#### Control group

Patients in the control group will receive treatment-as-usual and will also be assessed for 12 months. After the baseline visit in which all the variables of the study will be collected, follow-up visits will be carried out every 6 months.

#### Randomization

The randomization will be made using the block randomization technique. The blocks consist of 4 patients, two subjects per group [Intervention (I) and control (C)]: (IICC); (CCII); (CICI); (ICIC); (ICCI); (CIIC). The blocks will be marked with a number from 1 to 54 and they will be chosen at random to create the allocation sequence using a sequence of random numbers generated by the Microsoft Excel program with the function fx:RAND().

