### Setting

Patients will be identified from people with self-perceived cognitive impairment or caregiver’s perception of cognitive impairment that has been present for more than 6 months and who meet all the study eligibility criteria. The patients can be under primary care services, as well as, secondary care services, such as those who are being followed up in memory clinics, outpatient clinics, day hospitals or other components of specialist mental health, geriatric medicine and neurology services. The clinicians involved in identifying the patients will be physicians (primary care, psychiatry, neurology, and geriatrics), neuropsychologists and dementia and mental health nurses.

The identification process by the clinician will consist of screening, using information gathered from medical notes, clinical records and/or clinical consultations, for initial eligibility based on inclusion criteria. Patients will receive a brief explanation by their clinician. A member of the research team will contact the patient to see if they are willing to participate in the study, and if so, an appointment at their referral centre will be scheduled. Their primary caregiver must attend this visit.

At this first visit, the researcher will determine the patient’s eligibility and will explain the study in detail and answer any questions the patient or caregiver may have. After doing so, the patient’s ability to consent will be assessed following the Assessment of capacity to consent which includes the 5 fundamental principles of the Mental Capacity Act. In case of cognitive impairment or dementia, patients will be asked five questions regarding the information received as part of the decision-making process. Proxy consent of a legal representative or the caregiver will be required when the patient is not found capable. Both the patient and caregiver will give consent regarding their participation in the study. Once given consent, the patient will be randomized into the intervention or control group. Follow-up will begin after the randomization and will be determined by the group allocation. Within one to two weeks after being included in the study, patients allocated in the intervention group will be scheduled a visit for TV-AssistDem installation and training.

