### Participants

Two hundred forty participant dyads in two European countries (Spain and Romania). The participant dyads will comprise the PMCI/MD and their informal caregivers, defined as the person who is unwaged for this role and who spends the most time with the patient and whom the patient declares that he/she is his/her informal caregiver, for care or support of care, and who does not take part in a formal network of organized care.

A patient will be eligible for inclusion in this trial only if all following criteria apply:
Patients are over sixty years of age.Self-perceived cognitive impairment or caregiver’s perception of cognitive impairment that has been present for more than 6 months.Patients score 23–27 points on Mini-Mental State Examination (MMSE).Patients live independently.Patients have an informal caregiver.Patients who take pharmacological treatment for chronic conditions during study period and are in charge of their own medication.The place where patients live has enough wireless or phone network connectivity to enable them to use TV-AssistDem platform on a daily basis.Patients agree to be part of the study by giving signed written consent.

A patient will not be eligible for inclusion in this trial if any of the following criteria apply:
Patients score above 11 on the Geriatric Depression Scale (GDS-15).Patients have a terminal illness with less than 3 years expected survival.Patients have specific conditions reducing their physical ability to use the application to a point that makes their participation in the project impossible (the nature of the conditions will be recorded in such cases).

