#### Sample size

The main outcome measure is the total score of the QoL-AD, which ranges from 13 to 52. According to recent studies [40, 41], the standard deviation of the total score of the QoL-AD is 7.

For a minimum important clinical difference of 2.77 on the total QoL-AD score, with a standard deviation of 7, the effect size is 0.39. To compare two groups (Intervention and Control) using a two-sample, two-sided t-test with a 5% statistical significance level, the minimum number of evaluable patients required in each group is 100 (200 overall), to give a power of 80%. Given that it is a follow-up study, we must bear in mind that there will be losses along this one, therefore we will recalculate the sample size to take into account an expected percentage of losses of 20%. The number of subjects needed for each group will be 120 subjects (240 in total).

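### As written, the allocation sequence of 54 blocks of 4 gives 216 assignments, 24 short of the 240 patients the protocol plans to randomise

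*Protocol article*

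**What the plan says.** The Randomization section of the protocol article sets the block size and the ratio within blocks: "The blocks consist of 4 patients, two subjects per group". It lists the six possible orderings of two intervention and two control places. It then gives the number of blocks and their use: "The blocks will be marked with a number from 1 to 54 and they will be chosen at random to create the allocation sequence". The random numbers come from the spreadsheet function RAND().

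The planned sample is stated consistently elsewhere. The Sample size section concludes: "The number of subjects needed for each group will be 120 subjects (240 in total". The Participants section gives "Two hundred forty participant dyads in two European countries (Spain and Romania", and the Methods part of the Abstract repeats 240. The Setting section makes the individual patient the unit of allocation: "Once given consent, the patient will be randomized into the intervention or control group".

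The article mentions no separate list for each country or centre, no stratification, no reuse of blocks and no rule for going beyond block 54.

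**The concern.** The block size and the number of blocks together fix how many patients the sequence can allocate, and that number does not match the planned sample. This is not a detail that a condensed article leaves to a fuller document: both numbers are printed, and they disagree.

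What is at stake depends on what happens when the sequence runs out. If enrolment stopped there, the trial would fall below its own sample size and lose some power. If places were added during recruitment, the final tenth of the sample would be allocated by a procedure that the plan does not describe.

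**Working it through.** **Inputs**
- Block size 4, two per arm; 54 blocks (Randomization).
- Planned total 240, 120 per group; 100 evaluable per group; expected losses 20% (Sample size).
- Difference 2.77 and SD 7: "For a minimum important clinical difference of 2.77 on the total QoL-AD score, with a standard deviation of 7, the effect size is 0.39".
- Test: "using a two-sample, two-sided t-test with a 5% statistical significance level", with 80% power.

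**Step 1. Reproduce the plan's sample size.**
- Standardised difference: 2.77 / 7 = 0.396.
- Normal approximation: n per group = 2 × [7 × (1.960 + 0.842) / 2.77]² ≈ 100.2. The exact t-test gives 101.2.
- Both agree closely with the stated 100. Power at 100 per group is 79.5% by the t-test (79.9% by the normal approximation).
- The stated total follows as 100 × 1.20 = 120 per group, 240 in all.

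**Step 2. Capacity of the sequence, each numbered block used once.**
- 54 × 4 = 216 assignments; 216 / 2 = 108 per group.
- Shortfall: 240 − 216 = 24 patients, 12 per group; 24 / 240 = 10%.
- Blocks needed: 240 / 4 = 60, six more than stated.

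**Step 3. Power if enrolment stopped at 216.** The same 20% losses are applied to both totals, so that only the block shortfall differs.

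| Randomised | Evaluable (× 0.80) | Per group | Power, t-test | Power, normal approx. |
|---|---|---|---|---|
| 240 | 192 | 96 | 77.9% | 78.3% |
| 216 | 172.8 | 86.4 | 73.4% | 73.9% |

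The shortfall itself costs about 4.4 percentage points (77.9% to 73.4%).

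The planned 240 already falls somewhat below 80% because losses are allowed for by multiplying by 1.2. Dividing by 0.8 would give 100 / 0.80 = 125 per group. That is a separate matter and is not counted here.

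**Step 4. Readings that would remove the shortfall.**
- One 54-block list in each of the two countries: 2 × 216 = 432 places.
- A pool of 54 numbered blocks (54 / 6 = 9 copies of each ordering), drawn from repeatedly until 240 places are filled.

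Nothing in the article states either one.

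**The case against.** The strongest reply is that the Randomization section is a short summary and that 54 need not be the length of the sequence. Fifty-four is an exact multiple of the six orderings, so it could be a pool to draw from. There are also two centres, so each could hold its own list. This stands in part: a single list with each block used once is the plain reading but is not spelled out. A reader might therefore infer that the last 24 patients will have no randomised allocation, and the text does not establish that. Even so, the two sections do not agree as printed, and under either alternative a sentence is still needed to say so.

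A second reply is that a short list is easily extended: six more blocks made with the same RAND() procedure would leave those patients properly randomised. This also stands. A reader might infer that the final places would be improvised by staff who had seen the earlier assignments. The article does not say who generates or holds the list, or what that person sees. Assignments are likely to be evident in practice, since one arm has a device installed at home and the other has usual care, but that makes a late extension a risk and nothing more.

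A third reply concerns size. It is tempting to set the 73% against the nominal 80% and report a loss of seven points. That comparison mixes two effects, because 80% belongs to 100 evaluable per group, whereas the planned 240 with 20% losses leaves 96. The like-for-like loss is about four points. Stopping at 216 would also contradict the total of 240 given in three places, so that scenario is conditional.

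**Conclusion.** The inconsistency holds. The sequence as described provides 216 assignments against 240 planned, a gap of 24 patients or 10%. That part is plain arithmetic on the article's own figures and assumes only one list with each numbered block used once.

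The consequences are conditional. If enrolment ended with the list and losses were 20% spread evenly over the groups, power would be about 73% against about 78% for the full 240, given the protocol's difference of 2.77 and SD of 7. If the list were extended during recruitment, the validity of the last 24 places would depend on a step the plan leaves undescribed.

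The estimand, the analysis model and the stated sample size are unaffected. The point still needs correcting, because the randomisation relies on this number and the correction is almost free.

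**What to change.** Before recruitment opens, generate a sequence covering at least 240 patients (60 or more blocks of 4) and replace 54 in the Randomization section with the number actually used. If the sponsor intended separate lists by country or repeated drawing from a pool of 54, keep the number and add a sentence saying how the 54 blocks cover 240 patients. Either way, the Randomization and Sample size sections should then agree.

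The cost is a few minutes to regenerate the list and a correction of one number or one sentence. If a longer or per-country list already exists, only the text needs changing.

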### Statistics

The flow of individuals will be shown schematically with counts and percentages in a CONSORT diagram. The analysis will be made following an intention-to-treat procedure. All variables collected will be summarized by group and by site at baseline and at final follow-up. Statistics considered for presentation for continuous measures in summary tables will be the mean, minima and maxima, and standard deviation, and if the criteria of normality are not met, the median and the first and third quartiles. Categorical variables will be summarized using counts and percentages. The baseline variables of the experimental group and the control group will be compared using the Chi-Square test for categorical variables and analysis of covariance for continuous variables.

For the primary outcome, a Linear Mixed Model analyses will be carried out as this approach is optimal to include subjects with missing data. First, an unadjusted analysis will be carried out and secondarily, in case that potentially confusing factors differ between the experimental group and the control group, despite the randomization, a supplementary multivariate analysis will be carried out. For secondary outcomes a Linear Mixed Model and Generalized Mixed Model analysis will be used for continuous and categorical variables respectively. Analysis will be two-tailed and alpha level set at 0.05.

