**Methods:**

This is a 12-month European multicentre randomized controlled trial which will be performed in two countries: Spain and Romania. Two hundred and forty older adults will be recruited using identical inclusion/exclusion criteria. The primary outcome will be the change from baseline of TV-AssistDem on patient quality of life at 12 months. The secondary outcomes will be the changes from baseline of: 1) informal caregiver quality of life, 2) informal caregiver burden, 3) patient treatment adherence, 4) patient treatment compliance, 5) patient functional status, and 6) healthcare cost-effectiveness at 12 months. Patients in the intervention group will have access to an interactive platform which offers remote assistive services through a device connected to the television. The core services of the platform are: 1) Calendar and reminders, 2) Health monitoring and data transmission to a health server and 3) Videoconference; service-oriented applications are: 4) Cognitive stimulation; 5) Reminiscences; and 6) Patient and caregiver healthcare education. The analysis will be made following an intention-to-treat procedure. Linear and Generalized Mixed Model analysis will be performed.

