### Outcome measures

The primary outcome measure is the change in patient quality of life measured with the Quality of Life-Alzheimer’s Disease Scale (QoL-AD) [19–22]. Additional assessments will be used for secondary outcomes: caregiver quality of life and burden, patient treatment adherence and compliance, patient functional status and service utilization. TV-Assist Dem usability and other covariables will also be collected.

Patients will be assessed at baseline and at 6 months and 12 months after the beginning of the intervention. The assessments will be conducted under standardized conditions at the study centres.

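### Adjustment of the QoL-AD analysis should be prespecified on baseline QoL-AD, not run as a supplement only when baseline factors happen to differ

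*Protocol article*

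**What the plan says.** The abstract defines the endpoint as a change: "The primary outcome will be the change from baseline of TV-AssistDem on patient quality of life at 12 months". Outcome measures agrees ("The primary outcome measure is the change in patient quality of life measured with the Quality of Life-Alzheimer’s Disease Scale (QoL-AD") and sets three assessments: "Patients will be assessed at baseline and at 6 months and 12 months after the beginning of the intervention".

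The Statistics section names the method: "For the primary outcome, a Linear Mixed Model analyses will be carried out as this approach is optimal to include subjects with missing data". It then fixes the order of analyses: "First, an unadjusted analysis will be carried out and secondarily, in case that potentially confusing factors differ between the experimental group" and, after naming the control group, "despite the randomization, a supplementary multivariate analysis will be carried out". It lists no factors and gives no threshold for deciding that groups differ. The paragraph before it plans between-arm comparisons at baseline ("The baseline variables of the experimental group and the control group will be compared using the Chi-Square test" for categorical variables, analysis of covariance for continuous ones).

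The Sample size section uses a two-sample t-test and a variability figure for the score itself: "the standard deviation of the total score of the QoL-AD is 7". It gives neither an SD of change nor a correlation between baseline and 12 months.

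**The concern.** There are two linked problems.

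**The trigger.** In a randomised trial, observed baseline differences arise by chance. A covariate earns its place by predicting the outcome, and imbalance between arms does not show that. Under this rule, chance decides whether an adjusted estimate appears beside the unadjusted one, and which covariates it uses. A reader could then face two estimates of the primary effect with no prior statement of how the second was to be built.

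**Precision.** Baseline QoL-AD is collected from every patient and is a natural predictor of QoL-AD at 12 months. If the lead analysis is a plain comparison of change, its power depends on r, on which the article is silent. Adjusting for baseline removes most of that dependence.

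**Working it through.** **Inputs.** From Sample size: difference 2.77, SD 7 (total score), two-sided 5%, 100 evaluable per group, 80% power. From the abstract: endpoint is change at 12 months. Assumed, because the article gives none: r from 0.3 to 0.7, with equal SDs at baseline and 12 months.

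**Step 1: the plan's own figure.** n per group = 2 × (1.96 + 0.842)² × 7² / 2.77² = 100.2, so 101 by the normal approximation (102 by the exact t-test). Power at 100 per group is 79.9%. The stated 100 reproduces.

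**Step 2: SD under each analysis.**
- Unadjusted change: 7 × √(2(1 − r)). This equals 7 only at r = 0.5.
- Adjusted for baseline: 7 × √(1 − r²). This never exceeds 7.
- Ratio of variances, and so of sample sizes: 2(1 − r)/(1 − r²) = 2/(1 + r).

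**Step 3: power at 100 per group** (normal approximation), and n per group for 80%.

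| r (assumed) | SD, change | Power | n | SD, adjusted | Power | n | 2/(1+r) |
|---|---|---|---|---|---|---|---|
| 0.3 | 8.28 | 65.7% | 141 | 6.68 | 83.5% | 92 | 1.54 |
| 0.4 | 7.67 | 72.4% | 121 | 6.42 | 86.3% | 85 | 1.43 |
| 0.5 | 7.00 | 79.9% | 101 | 6.06 | 89.8% | 76 | 1.33 |
| 0.6 | 6.26 | 87.9% | 81 | 5.60 | 93.8% | 65 | 1.25 |
| 0.7 | 5.42 | 95.1% | 61 | 5.00 | 97.5% | 52 | 1.18 |

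The planned 100 evaluable is used throughout, so that the allowance for losses, a separate matter, does not enter the comparison.

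**Step 4: how often chance would trigger adjustment.** If k independent factors were each tested at 5%, the probability of at least one spurious difference is 1 − 0.95^k: 23% for k = 5, 40% for k = 10, 64% for k = 20. The Covariables section lists ten items. Independence and the 5% threshold are assumptions, since the article states no criterion.

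**Step 5: does conditional adjustment recover the precision?** Simulation of 20,000 trials, 100 per group, switching to baseline adjustment only when the baseline QoL-AD test gives p < 0.05:

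| r | Change score | Switch if baseline differs | Always adjusted |
|---|---|---|---|
| 0.3 | 65.2% | 66.5% | 82.5% |
| 0.5 | 79.8% | 81.0% | 89.5% |
| 0.7 | 95.0% | 95.3% | 97.4% |

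Almost nothing is recovered. With no true effect, the switching rule rejects in 3.9%, 4.4% and 4.6% of trials. Taking the smaller of the two p-values when both exist gives 5.0% to 5.2%.

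**The case against.** Several stronger readings are tempting, and the article does not support them.

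- **That chance picks the primary model.** It does not. The unadjusted analysis always comes first and the adjusted one is labelled supplementary. Nor does Step 5 show any material inflation of type I error.
- **That the primary model discards baseline QoL-AD.** The article does not list the response vector or the fixed effects, which it may properly leave to a fuller document. A mixed model called unadjusted can carry baseline as a response. With a common baseline mean it is about as efficient as covariate adjustment; with arm-specific means and complete data it equals the change score. The text does not say which is meant.
- **That the trial is underpowered.** This depends on an unknown r. Above about 0.5 the change score exceeds the planned power. The Sample size section is also consistent in itself, taking both the difference and the SD on the total score. A t-test on completers only approximates a mixed model that also uses 6-month and partial data.
- **That omitting country is costly.** No loss can be calculated from the article, and the Randomization section states no stratification by country.
- **That the baseline tests are the formal trigger.** This is a fair inference from their position, but the text says only that factors differ.

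It is also true that an unadjusted comparison in a randomised trial is unbiased and valid. What stands is that the conditional rule is written into the article rather than left open, and that an unadjusted lead analysis is never more efficient than a baseline-adjusted one.

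**Conclusion.** The point holds in limited form and should be fixed; it does not threaten the validity of the primary result. The rule lets chance decide whether a second estimate of the primary effect appears and which covariates it uses. It also forgoes precision unless the mixed model already constrains baseline means to be equal. For r between 0.3 and 0.7, an unadjusted change comparison needs 1.54 down to 1.18 times as many patients as a baseline-adjusted one. The gain in power from adjustment is about 18 percentage points at r = 0.3, 10 at r = 0.5 and 2 at r = 0.7. These sizes rest on the assumed r, on equal SDs at the two visits, and on reading SD 7 as the total-score SD, as the article words it.

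**What to change.** In Statistics:

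- Prespecify one primary linear mixed model for QoL-AD at 6 and 12 months in all randomised patients, with arm-by-visit terms and adjustment for baseline QoL-AD. Keeping baseline in the outcome vector with a common mean across arms is an equivalent choice.
- Name the 12-month contrast between arms as the primary estimate. Country may be added as a further prespecified term.
- Report the unadjusted model as a sensitivity analysis.
- Delete the rule that observed differences lead to adjustment, and present baseline data descriptively without between-arm tests.

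In Sample size, state that SD 7 is the cross-sectional SD of the total score and is conservative for the baseline-adjusted analysis.

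The cost is wording only. Every variable needed is already collected, and the planned number of patients does not change on this account.
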